#### Data Collection

The displayed HR from the HRD and the PO or ECG monitor will be video recorded for 3 minutes within the same video frame, as shown in Figure 1. Video recording will take place using a dedicated research digital camera mounted on a stand. Video recording will start once the infant is settled and the PO or ECG readings are stable. Stable readings are defined based on the device’s instructions on waiting for an appropriate amount of time after sensor placement for clinical HR determination. The HRD will then be placed on the infant’s chest until a consistent HR is displayed for 3 minutes, at which point video recording will start. After 3 minutes, the HRD will be removed, and then, the recording will be stopped. After the recording is completed, the entire HRD, including electrodes, will be wiped down with a surface disinfectant towelette (CaviWipe; Metrex). HRD device failure will be considered if no HR is displayed on the HRD within 60 seconds of application to the thorax.

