### Study Personnel

A pediatrician and graduate student will be conducting all the study tasks.

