#### Data Management

Video recordings will be individually analyzed by 2 health professional researchers to determine the time it takes to apply the HRD to the thorax and the time from HRD placement to a steady HR display. Each researcher will review and record the HR from the HRD and PO or ECG at 2-second intervals for 3 minutes, providing approximately 90 HR notations per device per patient. For 50 newborns, the total number of HR annotations will be approximately 4500 data points. This will result in multiple HR data points to compare. To avoid human error in the annotation process, discrepancies in the HR of more than 5 beats per minute between the 2 researchers will lead to a reexamination of the video recordings until a consensus can be reached regarding the correct HR. The annotations from the 2 researchers will be averaged for the subsequent analyses.

Additionally, the HRD will record raw ECG signals for the duration of the device being in contact with the infant. Raw ECG data will be collected at 500 Hz sampling rate and transmitted to a research-dedicated laptop. The raw ECG and HR information from the HRD will be stored on different CSV files with a randomized identification number.

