#### Data Analysis

HR and raw ECG data will be analyzed using MATLAB (the MathWorks). Infant demographics will be analyzed using summary statistics. Continuous variables will be expressed as mean (SD) values, and categorical variables will be expressed as numbers (percentages), unless otherwise stated. The HR from HRD will be compared to PO or ECG using a paired *t* test. The Bland-Altman method will be used to compare the HR derived from each device—the HRD and the PO or ECG monitor, used as reference. The correlation between devices will be assessed using Pearson *r* statistic. Data will be first analyzed using all data points available, and outliers will be defined as 20 beats per minute rate difference between the methods. These discrepancies will be further analyzed to find the likely reason for deviation, including reexamination of the video recordings.

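### Two readers take both heart rates, and judge when the new device is steady, from video showing both values with no masking stated, so the readings are open to bias

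*Protocol article*

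**What the plan says.** Four parts of the protocol article's Methods fix the reading procedure.

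- **Data Collection, how it is filmed:** "The displayed HR from the HRD and the PO or ECG monitor will be video recorded for 3 minutes within the same video frame". The reference is pulse oximetry (PO) or 3-lead ECG.
- **Data Management, who reads what:** "Video recordings will be individually analyzed by 2 health professional researchers". Then: "Each researcher will review and record the HR from the HRD and PO or ECG at 2-second intervals for 3 minutes". Each reader therefore records both the test device and the reference. The same readers also determine "the time from HRD placement to a steady HR display".
- **Data Management, checks:** "discrepancies in the HR of more than 5 beats per minute between the 2 researchers will lead to a reexamination of the video recordings", continuing until they agree. After that, "The annotations from the 2 researchers will be averaged for the subsequent analyses". The section also says that the HRD's own HR is stored in CSV files. It describes no electronic log of the reference HR.
- **Data Analysis:** "outliers will be defined as 20 beats per minute rate difference between the methods", and these pairs are looked at again, including on the video.

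Nothing in these sections says that one display is hidden while the other is read, and no numeric rule for a steady display is given.

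**The concern.** In a method-comparison study the test device is best read without sight of the reference, and the reference without sight of the test device. Here one person sees both numbers and writes both down. Where a frame is unclear or a digit is changing, the other display is an available cue, and it favours agreement.

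The timing outcome is more exposed. A displayed number is copied, but steadiness is judged. A reader who can see the reference may decide that the HRD is steady because it matches, rather than because its own display has settled.

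Two of the four research questions under Objectives depend on these readings: how accurate the HRD is against PO or ECG, and how fast it detects HR. The article describes the reading procedure in some detail (readers, interval, discrepancy threshold, consensus, averaging), so the paired view is part of the stated procedure and not merely a detail left out.

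**Working it through.** **1. The plan's own count.** Inputs from Data Management: 3 minutes, one reading every 2 seconds, 50 newborns.

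- 180 s / 2 s = 90 readings per device per infant
- 90 x 50 = 4500

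Both figures reproduce. The 4500 are paired time points, and separate reading would not change that number.

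**2. What the between-reader check can catch.** Re-examination needs a difference of more than 5 bpm between the readers.

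- One reader correct, the other off by 5 bpm: the difference is 5, no review follows, and the average moves by 5 / 2 = 2.5 bpm.
- Both readers shifted by the same amount x: the difference is 0, no review follows, and the average moves by x.

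The check guards against one reader's slip. It does not guard against a cue that both readers see. When it is triggered, consensus is reached on the same recordings, which show both displays.

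**3. What the between-method review covers.** Data Analysis names only pairs 20 bpm apart for a second look at the video. Concordant pairs get none, so any correction that followed could act only on disagreements. The section does not say that values will be changed.

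**4. Possible size for the HR values.** The documents give no SD of the device differences and no frequency of unclear frames, so these inputs are assumptions:

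- the HRD-minus-reference difference is normal with mean 0 and SD 5 or 8 bpm;
- 5% to 25% of time points are ambiguous between two candidate values 1 to 5 bpm apart;
- a masked reader picks one of the two at random;
- an unmasked reader always picks the value nearer the other device, which is the worst case.

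Half-width of the limits of agreement = 1.96 x SD of the recorded differences (400,000 simulated differences per setting):

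| SD (bpm) | Gap (bpm) | Ambiguous | Masked | Unmasked | Difference |
|---|---|---|---|---|---|
| 5 | 1 | 5% | 9.79 | 9.75 | 0.04 |
| 5 | 3 | 10% | 9.87 | 9.62 | 0.25 |
| 5 | 5 | 25% | 10.38 | 9.30 | 1.08 |
| 8 | 1 | 5% | 15.67 | 15.63 | 0.04 |
| 8 | 3 | 10% | 15.74 | 15.50 | 0.24 |
| 8 | 5 | 25% | 16.02 | 14.98 | 1.04 |

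Part of the gap is noise added by random picking. Against no ambiguity at all, the two extreme settings narrow by 9.79 - 9.30 = 0.49 and 15.68 - 14.98 = 0.70 bpm.

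**5. Time to steady HR.** No arithmetic applies. The outcome is judged from video planned to show both values, and the article gives no numeric rule. A reader could call the display steady early, when the numbers first match, or late, by waiting for a match after the HRD has already settled. The direction is open.

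**The case against.** The strongest reply is that the readers transcribe and do not interpret. The HRD shows digits on a screen, and the reference monitors compute and display their own HR. Sight of one legible number does not alter another. This largely stands, and it confines the risk for HR values to ambiguous or changing frames.

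Filming both devices together time-matches the readings and is a strength. That also stands: the weakness lies in reading the two together, not in filming them together. A condensed article may also leave reading order to the full protocol. That tempers the point, but the procedure as published has each reader take both devices from the paired video.

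Stronger conclusions that a reader might draw are not supported:

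- **Readers can choose any value within each 2-second step.** The plan describes readings at time points, not a window to select from.
- **A shift could never be found.** The HRD's stored HR would allow its annotations to be checked without a reader. The plan does not say that it will be used so, and describes no such log for the reference.
- **The readers are the people who applied the device.** Study Personnel says "A pediatrician and graduate student will be conducting all the study tasks", while Data Management refers to two health professional researchers. That they are the same two people is an inference.

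Finally, masking does not supply a definition of steady. Nor does it settle whether recording starts before HRD placement or after a consistent display, both of which Data Collection describes. Those are separate matters.

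**Conclusion.** The point holds as a risk of bias. The displays are filmed together, the same two readers record both and judge steadiness, and no masking is stated. The stated checks would not catch both readers leaning the same way.

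For HR values the effect is probably small: about 0.04 to 1.1 bpm per side of the limits of agreement. That range rests wholly on the assumed SDs and ambiguity rates and on readers who always choose the nearer value. For time to steady HR the size cannot be given. It would be tempting to say that unmasked reading shortens this time, or that the agreement results are biased, but the documents show neither. The change is worth making because it is cheap and protects both the accuracy and the speed outcomes.

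**What to change.** 1. Keep filming both displays in one frame, for time-matching.
2. Crop or mask each video into an HRD-only clip and a reference-only clip on a common time code. The HRD-only clip should still show the moment of placement.
3. Have the same two readers annotate the clips in separate passes, and lock each device's set before the two are merged.
4. Resolve differences between readers on the masked clip, not on the paired picture.
5. Judge time to steady HR from the HRD-only clip.
6. Compare the HRD annotations with the HR stored in the HRD's CSV file.

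The cost is video cropping and a second reading pass by the same two readers. No extra infants, staff or bedside procedures are needed, and it can be applied to videos already recorded.

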## Abstract

**Background:**

Over 10 million newborns worldwide undergo resuscitation at birth each year. Pediatricians may use electrocardiogram (ECG), pulse oximetry (PO), and stethoscope in determining heart rate (HR), as HR guides the need for and steps of resuscitation. HR must be obtained quickly and accurately. Unfortunately, the current diagnostic modalities are either too slow, obtaining HR in more than a minute, or inaccurate. With time constraints, a reliable robust heart rate detector (HRD) modality is required. This paper discusses a protocol for conducting a methods-based comparison study to determine the HR accuracy of a novel real-time HRD based on 3D-printed dry-electrode single-lead ECG signals for cost-effective and quick HR determination. The HRD’s HR results are compared to either clinical-grade ECG or PO monitors to ensure robustness and accuracy.

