### Study Significance and Impact

Given that no single method of HR assessment is clearly superior to others, finding the optimal method to delineate HR within the golden minute after birth remains elusive. Pediatric guidelines recognize this knowledge gap and identify the opportunity to develop new technologies for the rapid, accurate assessment of HR after birth, ideally integrating newborn ECG. Currently, there are no novel medical devices that have been specifically developed to provide rapid and accurate HR immediately after birth. The proposed research study will address several gaps in the scientific study of device development, vital signs measurement and monitoring, and neonatal resuscitation. Recent advances in biomedical sensors and wireless communication technologies have enabled us to develop a novel HRD, targeted to outperform the traditional HR assessment in neonatal resuscitation. The rapid application, measurement, and display of HR on a device located on the neonate addresses significant gaps in the provision of optimal neonatal resuscitation. The HRD is undergoing rigorous design and development, and this study aims to assess its feasibility in quickly detecting accurate HRs in infants using 3D-printed dry electrodes. This early proof-of-concept HRD study will establish the basis for using 3D-printed dry electrodes and determine whether novel HR estimation algorithms are appropriate for neonatal HR applications.

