## Methods

### Study Design

A prospective observational study will be used to measure the performance of the HRD prototype, as shown in Figure 1, in terms of time required to place it on an infant, its ability to detect HR, the speed of detection, and its reliability (accuracy) in comparison with clinical HR monitors. Given the paucity of data on infants regarding the HRD, there is insufficient evidence to support the feasibility and performance of a randomized controlled trial. The study setting will be in the postpartum unit (PPU) and neonatal intensive care unit (NICU) of a large community teaching hospital in Toronto, Canada. Specifically, the study will take place within 2 physical settings at the hospital: PPU and NICU. As shown in Figure 2, a digital camera will be used to record the HRD concurrently with either an ECG or PO monitor, depending on their availability at the time, for 3-minute durations per newborn. It is important to note that although both 3-lead ECG or photoplethysmogram technology are compared to single-lead dry-electrode ECG, both clinical devices are considered acceptable for neonatal resuscitation efforts, which is the targeted use of the HRD in later versions and research studies.

The HRD uses two 3D-printed dry electrodes to collect 3-minute single-lead neonatal ECG signals with a 500 Hz sampling rate. The HRD’s electrodes are placed approximately in the V1 and V2 locations on the newborn’s chest, as shown in Figure 3. The electrodes are developed using conductive polylactic acid filaments (Proto Pasta) and a 3D printer with printing settings of nozzle temperature at 215 °C, print speed of 35 mm/s, heated bed temperature of 60°C, and a design fill ratio of 100% [15]. These settings are chosen as specified under the datasheets provided for the conductive polylactic acid filament. As shown in Figure 4, the electrodes are connected to an ECG analog front-end circuitry, which provides analog signal processing and filtering. A 3-48 Hz analog bandpass filter is applied to attenuate the powerline and electromagnetic interference noise in the 50-60 Hz range [15]. The single-lead ECG signal is later transmitted to a microcontroller, where patent-pending embedded heart estimation techniques are used to calculate HR. HR is displayed on an OLED screen on the HRD. At the same time, the HR and raw ECG information are transmitted using Bluetooth to a nearby computer interface for data storage.

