### Study Procedures

The PPU infants will be placed in the supine (face up) position. The conventional PO will be connected to the right hand as per the device’s instructions and CCHD screening protocol. In the usual standard of care for CCHD screening, PO is placed on the right hand and right or left foot for 1 to 2 minutes. The change in the standard of care will include the data collection protocol during the time of CCHD screening, which includes video recording of the HRD and PO simultaneously. The HRD will be held in place by a pediatrician on the thorax for 3 minutes. This will prolong CCHD screening by an additional 1-3 minutes. On the other hand, as per the usual standard of care, NICU infants will be placed in the supine (face up) position prior to their usual feeding time; they will be unbundled and have their diaper changed. An already attached conventional 3-lead ECG will be placed on the infant’s chest, as per the conventional 3-lead ECG device’s instructions. The change in this standard of care will involve the thorax to be exposed, if not already exposed, and the HRD will be held in place by a pediatrician on the thorax for 3 minutes during simultaneous video recording of the HRD and the 3-lead ECG monitor. It is important to note that the 3-lead ECG electrodes will not be in contact with the HRD’s dry electrodes.

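### The video starts too late to time the pulse oximeter and, under the second of its two start rules, too late to time the HRD itself

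*Protocol article*

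**What the plan says.** Data Collection gives two start points for the recording.

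- First: "Video recording will start once the infant is settled and the PO or ECG readings are stable". Stability is defined by the device's instructions on "waiting for an appropriate amount of time after sensor placement for clinical HR determination". The HRD is placed after that.
- Second: the HRD is held on the chest "until a consistent HR is displayed for 3 minutes, at which point video recording will start".

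The same section counts the HRD as failed if it shows no heart rate within 60 seconds of application.

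Data Management has two researchers take two times from the video, both for the HRD: the time to apply it, and the time from placement to a steady display. No reference time is listed. Data Analysis compares heart-rate values, not times.

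Study Procedures describes the reference in each unit. In the PPU, "The conventional PO will be connected to the right hand as per the device’s instructions and CCHD screening protocol". In the neonatal intensive care unit (NICU), the 3-lead ECG is already attached.

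Speed is central to the rationale. The Abstract says "the current diagnostic modalities are either too slow, obtaining HR in more than a minute, or inaccurate", and Study Significance and Impact describes work to "develop a novel HRD, targeted to outperform the traditional HR assessment in neonatal resuscitation". In Objectives, however, the question on speed names only the prototype; PO or ECG appears only in the question on accuracy.

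**The concern.** A device justified by being quicker than existing monitors will be studied without any concurrent timing of those monitors. In PPU infants the PO sensor goes on during the study visit, so its application and first display happen in front of the team. They go unrecorded because the camera is not yet required to run and because no reference time is on the annotation list.

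The only remaining comparison would be with the background statements. The Introduction says that PO takes several minutes to apply and first display, in a description of the delivery room. The study infants are at least 24 hours old, clinically stable, supine and settled, which is an easier setting for any sensor. Setting their HRD times against delivery-room PO times would probably flatter the HRD.

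The second start rule touches the study's own questions. If the camera runs only after the HRD has been reading consistently for 3 minutes, placement and time to reading are already past. Two of the four research questions, on placement time and on speed of detection, then lose their stated data source.

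**Working it through.** **The plan's own counts.** One reading every 2 s for 3 minutes gives 180 / 2 = 90 per device per infant, and 90 × 50 = 4500. Both match Data Management. They concern heart-rate values and do not affect this point.

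**What each start rule lets the video contain.**

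| Event | Camera starts when reference is stable | Camera starts after 3 minutes of consistent HRD reading |
|---|---|---|
| PO applied, first and stable heart rate (PPU) | missed | missed |
| ECG start-up (NICU) | none to record; already attached | none to record |
| HRD application | captured | missed |
| HRD placement to steady reading | captured | missed |

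Reference times are lost in all 50 infants under both rules. The HRD times that Data Management needs survive only under the first. The HRD's stored ECG and heart-rate files might recover its time from contact to reading, but not its application time.

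**Which rule fits the stated visit length.** Study Procedures puts usual PO placement at 1 to 2 minutes, the HRD hold at 3 minutes and the added time at 1 to 3 minutes.

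- A 3-minute hold that fully overlaps PO adds 3 − 2 = 1 to 3 − 1 = 2 minutes. With no overlap it adds 3. This reproduces the stated range.
- The literal second rule needs 3 minutes of consistent reading and then 3 minutes of video, at least 6 minutes of hold. That adds 6 − 2 = 4 to 6 − 1 = 5 minutes with full overlap and 6 with none, which does not match.

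So the second rule conflicts with Study Procedures as well as with Data Management.

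**Precision if PO were timed in PPU infants.** The article gives neither the PPU share of the 50 nor an SD for a paired time difference, so both are assumed here. Half-width of the 95% CI = t(0.975, n − 1) × SD / √n.

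| Assumed PPU infants | SD 15 s | SD 30 s |
|---|---|---|
| 15 | 8.3 s | 16.6 s |
| 25 | 6.2 s | 12.4 s |
| 35 | 5.2 s | 10.3 s |

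These figures show only that a paired summary could be informative. They do not predict the size of any difference.

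**The case against.** The strongest reply is that the protocol does not ask whether the HRD is faster than PO or ECG. Objectives, and the Abstract's conclusions, treat speed as a property of the HRD and compare only accuracy with the monitors. The intention to outperform current methods describes why the device was built, and the study calls itself an early proof of concept. This stands. A reader might infer a comparative speed objective from the Study Design wording, "the speed of detection, and its reliability (accuracy) in comparison with clinical HR monitors", but the comparison there attaches most naturally to accuracy. The documents do not support saying that a stated aim fails.

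Waiting for a stable reference is also right for the accuracy comparison, since the HRD should not be scored against a monitor that is still settling. Nor is the wait open-ended: it is tied to the manufacturer's instructions. Both points stand, and both are compatible with running the camera earlier.

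A reader might also expect a paired HRD-minus-PO time to remove the bias of comparing with delivery-room figures. It would only reduce it. PO is always applied first, under the screening protocol rather than for rapid heart-rate reading, and before the infant is settled. Device is therefore confounded with order and infant state, probably in the HRD's favour.

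Finally, HRD speed does have an absolute yardstick in the 60-second failure limit. That limit can show that the HRD is quick enough by its own standard, but not that it is quicker than PO. Multimedia Appendix 2, the data collection form, is not shown. A manual timing entry there cannot be excluded, but the article describes none.

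**Conclusion.** The point holds in a limited form. As written, no infant yields a reference time to heart rate, so no head-to-head speed result is possible. This is an avoidable loss only in PPU infants; in NICU infants with an ECG already attached there is no start-up time to measure. It limits what can later be claimed rather than breaking an objective.

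The conflict over when recording starts is the more serious part. Read literally, the second rule removes from the video the HRD times that answer the study's own questions, and it does not fit the stated visit length. It may be a slip of wording, but the article does not say which rule governs.

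These conclusions rest on the sequence of procedures in the article, not on the precision figures, which depend on an assumed PPU count and an assumed SD. The change is worth making because it is cheap and settles both problems.

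**What to change.** 1. Reconcile Data Collection with Data Management and Study Procedures, and state one start rule. In all infants the camera runs from before HRD placement to the end of the 3-minute reading. In PPU infants it runs from before PO connection.
2. Keep the 3-minute accuracy comparison restricted to the period after the reference is stable.
3. In PPU infants, annotate PO application, first heart rate and stable heart rate, using the same conventions as for the HRD. Report the paired HRD-minus-PO time descriptively with its confidence interval, and state that PO always comes first, under the screening protocol, and before the infant is settled.
4. In NICU infants with an already attached ECG, report HRD times alone.
5. Make no claim of superior speed by reference to delivery-room figures.

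The cost is slightly longer video and a few more annotations per infant, with no added procedure, staff or participants. The paired result may show a smaller advantage over PO in calm infants than the background suggests.

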### Objectives

The overall aim of this research study is to evaluate a novel HRD that may enable timely and appropriate neonatal resuscitation. This study is being completed using a phased sequential user-centered approach. We completed the first phase of this research to determine end-user requirements and preferences for HR assessment in neonatal resuscitation. This phase resulted in the current design and features of the HRD.

The second phase outlines the creation of the HRD conceptual design and proof-of-concept prototype to be used in the final phase of feasibility mentioned in this study.

In the final phase, the focus of this proof-of-concept research study is to examine the functionality, speed, robustness, and reliability of the prototype HRD.

Specific research questions to be answered through this phase are the following:

How long does it take to place the HRD on an infant?Can the prototype HRD detect the HR of newborns?How fast can the prototype detect the HR of newborns?How accurate is the HR detection when compared to PO or ECG?

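### The protocol gives two incompatible start points for the video; under one of them the two time outcomes are not filmed and the accuracy window opens on an already steady HRD reading

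*Protocol article*

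**What the plan says.** All references are to the protocol article.

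- **Data Collection, start rule A:** "Video recording will start once the infant is settled and the PO or ECG readings are stable". The HRD is applied after that.
- **Data Collection, start rule B,** later in the same paragraph: the HRD is "placed on the infant’s chest until a consistent HR is displayed for 3 minutes, at which point video recording will start".
- **Data Collection, length and stop:** the two displays "will be video recorded for 3 minutes within the same video frame", and "After 3 minutes, the HRD will be removed, and then, the recording will be stopped". The same section defines device failure separately, as no HR shown within 60 seconds of application.
- **Data Management:** two researchers analyse the videos "to determine the time it takes to apply the HRD to the thorax and the time from HRD placement to a steady HR display". They also read both displays every 2 seconds for 3 minutes, giving about 90 readings per device per infant and about 4500 for 50 infants. The HRD logs raw ECG while it is in contact with the infant.
- **Objectives:** the four research questions include how long placement takes and "How fast can the prototype detect the HR of newborns".
- **Study Procedures,** postpartum unit: "The HRD will be held in place by a pediatrician on the thorax for 3 minutes". Usual oximetry for critical congenital heart disease (CCHD) screening takes 1 to 2 minutes, and of the added procedure the section says: "This will prolong CCHD screening by an additional 1-3 minutes".

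**The concern.** One recording cannot begin both before the HRD is applied and after it has settled on a consistent reading. The choice decides which data exist.

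Under rule B, placement and signal acquisition happen before the camera runs, although the video is the named source for both time outcomes. The agreement sample is also selected on device performance. The comparison opens once the HRD is already reading consistently, so erratic start-up values do not reach the paired t test, the Bland-Altman analysis or the correlation. An infant in whom the HRD never settles contributes no pairs. Both effects make the device look better.

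The article states two procedures that cannot both be followed, so this is not detail left to a fuller document. Placement time that was never filmed cannot be reconstructed later.

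**Working it through.** **1. The plan's own count.** From Data Management: 3 min = 180 s, read every 2 s. 180 / 2 = 90 readings per device per infant, and 90 × 50 = 4500 per device. Both figures reproduce. They assume that all 50 infants give a full 3 minutes of paired readings.

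**2. What each start rule puts on film.**

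| Event | Rule A | Rule B, literal | Rule B, read as first consistent HR |
|---|---|---|---|
| HRD applied | filmed | not filmed | not filmed |
| First HR displayed | filmed | not filmed | not filmed, unless it is itself the first consistent HR |
| Interval from placement to steady HR | filmed | not filmed | not filmed (only its end) |
| Start-up readings | filmed | not filmed | not filmed |
| Dropouts in the 3 recorded minutes | filmed | filmed | filmed |

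Only rule A supplies what Data Management extracts. The loss under rule B does not depend on taking the 3-minute wait literally.

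**3. HRD contact time under literal rule B.** Contact = time to HR + 3 min of consistent display + 3 min of recording. The documents give no distribution for time to HR, so I take 0 to 60 s as an assumed range, 60 s being the failure limit.

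- At 0 s: 0 + 3 + 3 = 6 min.
- At 60 s: 1 + 3 + 3 = 7 min.

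Study Procedures states 3 min.

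**4. Added CCHD screening time,** assuming oximetry stays on throughout. Added time = HRD contact − usual oximetry time of 1 to 2 min.

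- Literal rule B, 6 min: 6 − 2 = 4 to 6 − 1 = 5 min.
- Literal rule B, 7 min: 7 − 2 = 5 to 7 − 1 = 6 min.
- Three minutes of contact: 3 − 2 = 1 to 3 − 1 = 2 min.

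The stated range is 1 to 3 min. Three minutes of contact fits it; literal rule B does not.

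**5. Reading count under rule A with 3 minutes of contact.** Pairs exist only once the HRD displays a value. At the 60 s limit, (180 − 60) / 2 = 60 pairs, or 30 fewer than 90. A filmed placement plus 3 minutes of contact also makes the video somewhat longer than 3 minutes. So rule A does not fit every stated figure exactly either.

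**6. Infants with no consistent HR under rule B.** The documents give no failure rate. At assumed shares of 5%, 10% and 20%, the pairs remaining are 4500 × 0.95 = 4275, 4500 × 0.90 = 4050 and 4500 × 0.80 = 3600.

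**The case against.** The strongest defence is that rule B is a drafting slip. Rule A comes first, Data Management assumes it, and Study Design and Study Procedures both describe 3 minutes of HRD signal or contact. On that view the 3-minute phrase in rule B is a misplaced statement of recording length, and the 6-minute figure describes nothing the investigators intend. This is plausible, and it makes the contact-time and screening-time figures conditional on the literal wording. It does not remove the conflict: a start at the first consistent HR still leaves placement and acquisition off the video.

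Several stronger readings are tempting, but the documents do not support them:

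- **That recording begins only once the HRD is steady, so no video can show placement.** Rule A stands in the same paragraph and says otherwise.
- **That dropouts and unstable readings never meet the reference.** Rule B conditions only the start of the window. Later dropouts and errors are recorded, all available points are analysed first, and differences of 20 beats per minute are re-examined.
- **That failure to detect is hidden.** It has its own definition, timed from application. What the article does not state is how failures enter the accuracy results.
- **That the missing start-up period invalidates a resuscitation claim.** The article reserves resuscitation use for later versions and studies, and enrols infants at least 24 hours old. Speed of detection is nevertheless a stated question here.
- **That the HRD log makes the video unnecessary.** Full-contact logging is stated for raw ECG. It may recover time to HR, but placement precedes contact and cannot be recovered from it.

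**Conclusion.** The point holds as an internal contradiction that needs correcting. The protocol gives two start rules, and following rule B on either reading removes the stated data source for two of the four research questions. It also opens the accuracy window on a steady HRD reading, a selection in the device's favour. The size of that bias cannot be calculated, because the documents give neither start-up error nor failure rates.

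The durations apply only to the literal wording of rule B: at least 6 minutes of contact against 3, and, if oximetry stays on, at least 4 to 5 minutes of added screening against 1 to 3. The document does not show which rule operators follow, so it cannot be concluded that the data are already lost or biased.

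**What to change.** 1. Delete start rule B. Start the camera once the reference is stable and before the HRD is applied, and run it without a break through the comparison window.
2. Define time zero as first skin contact. Read placement time, time to first HR and time to steady HR from the video.
3. Include paired readings from the first displayed HR in the agreement analysis, and report the steady-state window alongside.
4. If contact is 3 minutes, restate the figure of about 90 readings per device as a maximum.
5. Reconcile the contact, recording and added screening times across Study Procedures, Data Collection and Data Management.

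The cost is wording, slightly longer video, somewhat fewer paired readings per infant (60 rather than 90 if display takes the full 60 s), and possibly less favourable accuracy. For infants already recorded under rule B, the HRD log may recover time to HR. Their placement time should be reported as missing.
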